#### Multiple testing

IRRs for the primary and secondary outcomes will be reported with 95% CIs and Bonferroni-corrected p values.

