#### Primary outcomes

Receiving any own mother’s milk at discharge (exclusively or in combination with infant formula).Receiving any own mother’s milk on day 14 of life (exclusively or in combination with infant formula).Severe NEC requiring surgery or resulting in death.^26^

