#### Secondary outcomes

Exclusive feeding with own mother’s milk at discharge.Any NEC, including NEC not requiring surgery and not resulting in death.

### Data analysis strategy: workstream 1

After data cleaning, the number of infants with missing data across key variables will be tabulated and the total number of exclusions and final study population size determined. Descriptive statistics will be presented to summarise the distribution of baseline variables during each of the three study phases, separately for the EMNODN units (intervention group) and all other units in England and Wales (control group). Continuous variables will be reported with means and SDs, if shown to be normally distributed using a combined skewness and kurtosis test, or otherwise will be reported using medians and IQRs. Categorical variables will be reported with frequencies and percentages. P values for differences between the three time periods will be reported using the χ^2^ test or the Wilcoxon rank-sum test, as appropriate.

We will use ITS analysis to assess the impact of implementation of the care bundle on the outcomes listed above, as has been used previously in neonatal research.^27^ This is a strong quasiexperimental design which accounts for underlying trends in an outcome. If, for example, rates of NEC were already in decline prior to the implementation of the bundle, the ITS methodology will detect any additional impact of the bundle, above the background decline. It can also account for the impact of any other interventions or changes in population characteristics which might themselves impact outcomes.

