### Sample size calculation

Workstream 1: The ITS analysis will have approximately 90% power to detect an absolute increase of 20% in the prevalence of receiving own mother’s milk at discharge and 80% power to detect a 15% absolute increase (baseline prevalence approximately 55%, approximately 23 infants per month in the EMNODN from 2017 to 2019; national average c.60%). This target is comparable to the prevalence of own mother’s milk feeding in the best performing neonatal network—in 2021, the South London Neonatal Operational Delivery Network achieved a prevalence of 76% (range by unit 71–80%) of infants receiving own mother’s milk at discharge.^37^ In 21 neonatal units in the UK in 2021, over 75% of infants received own mother’s milk at discharge, with the highest performing unit achieving 86% prevalence.^37^

NEC is a rare occurrence (incidence approximately 7%, approximately 3 cases per month in the EMNODN from 2017 to 2019; national average c.5%), and there is also considerable monthly variability in incidence. Therefore, statistical power to detect small changes in the incidence of NEC will be more limited; we will be powered to detect approximately a two-thirds reduction in the incidence of NEC. In line with previous studies of less common neonatal outcomes,^27^ the point estimate will, however, give an indication of the effect of the care bundle, even if the CI around this point estimate crosses the null value.

Workstream 2: We aim to conduct 33 interviews with parents (either individuals or couples, 3 per EMNODN unit) and 33 interviews with HCPs (3 per unit) using a combination of convenience (self-selecting) and purposeful sampling approaches, the latter particularly to approach parents from underserved groups who usually hesitate to participate in research. These numbers are based on principles of maximum variation and theoretical data saturation, which is related to the sampling approach rather than the analysis.^38^ Preliminary analysis will inform whether we need to use a second strategy based on the notion of inductive thematic saturation^39^ and, in which case, we may need to conduct additional interviews.

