## Patient and public involvement

The study protocol has been co-produced with the EMNODN Parent Advisory Group and the parent-led charity NEC UK^40^ to ensure representation from those with lived experiences of NEC and its consequences, both in the neonatal unit and after discharge. The chair of NEC UK is a parent co-applicant and will lead patient and public involvement (PPI) activities. A second PPI representative will also be invited to join the Project Management Group.

The primary outcome of receiving own mother’s milk feeds at discharge was selected by the parents as being the most meaningful outcome for them, and, further to their advice, the emphasis on receiving information and support for breastmilk expression in the process evaluation and the plans to explore this in detail in the semistructured parent interviews were included in the study plan.

With the support of The Centre for Ethnic Health Research,^41^ a semistructured focus group discussion has been conducted with women representing different ethnic minority groups, all of whom had experience of having a preterm baby. This discussion focused on co-production of study documentation, particularly the participant information sheets and interview guides. A semistructured focus group discussion has also been conducted with HCPs working with preterm infants in the East Midlands. This discussion focused on the production of the interview guide for HCPs. Interested parties from both focus groups will be invited to validate qualitative analyses (respondent validation), comment on results and recommendations and review and revise the public-facing dissemination materials. A final parent-led dissemination meeting will be held within the EMNODN.

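### Holm-adjusted p values would control the same family-wise error as the planned single-step Bonferroni correction and never reject less, whichever outcomes form the family

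*Protocol article*

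**What the plan says.** The protocol article lists three primary outcomes: any own mother's milk at discharge, any own mother's milk on day 14, and severe NEC ("Severe NEC requiring surgery or resulting in death"). It lists two secondary outcomes: exclusive own mother's milk at discharge, and any NEC ("Any NEC, including NEC not requiring surgery and not resulting in death").

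The Multiple testing section is one sentence: "IRRs for the primary and secondary outcomes will be reported with 95% CIs and Bonferroni-corrected p values". It names the method but gives no divisor, significance level or stepwise procedure. It does not say whether primary and secondary outcomes are corrected jointly or separately. Nothing there says that the confidence intervals are corrected.

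For milk at discharge, the Sample size calculation section claims about 90% power for a 20-point rise; for the smaller effect it gives "80% power to detect a 15% absolute increase". It does not state the significance level or mention the correction. It says that power for NEC is more limited, with roughly a two-thirds reduction detectable.

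**The concern.** Single-step Bonferroni compares every p value with the strictest threshold, however many outcomes have already been shown to change. Holm relaxes the threshold after each rejection and keeps the same family-wise guarantee. The plan therefore gives up some power and gets nothing in return that the article mentions.

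The bundle acts on several related feeding outcomes, so more than one real effect is plausible, and that is when a step-down method helps. At stake is a true improvement, for instance in milk at discharge, which the Patient and public involvement section says "was selected by the parents as being the most meaningful outcome for them". It could miss the corrected threshold under Bonferroni when Holm would have declared it.

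**Working it through.** **Inputs.** There are three primary and two secondary outcomes (outcome lists). I assume a family-wise level of 0.05, two-sided, because the article gives only 95% intervals. The starting point is 80% power per improving outcome at unadjusted 0.05. This is an assumption; it equals the article's figure for a 15-point increase in milk at discharge.

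**The plan's own power figure.** The article gives "baseline prevalence approximately 55%, approximately 23 infants per month in the EMNODN from 2017 to 2019". Read as infants receiving milk, this means 23/0.55 = 41.8 infants per month. A step-only Poisson interrupted time series (80 months before, 9 after, linear trend, seasonality, an assumed lockdown indicator, dispersion 1, no autocorrelation) has non-centrality 2.81 for 55% to 70%. That gives 80.3% power at unadjusted 0.05, which matches the stated 80%. For 55% to 75% the same model gives 95.8%, not about 90%, so the two stated figures are not reproduced together. Only the 80% is used below.

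**Bonferroni, by formula.** Power at level 0.05/m is Φ(δ − z), where z is the normal quantile at 1 − 0.05/(2m) and δ = 1.960 + 0.842 = 2.802.

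- m = 3: level 0.0167, z = 2.394, power = Φ(0.408) = 66%.
- m = 5: level 0.01, z = 2.576, power = Φ(0.226) = 59%.

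**Holm.** Order the p values. With five outcomes, compare the smallest with 0.05/5 = 0.01, the next with 0.05/4 = 0.0125, then 0.05/3 = 0.0167, 0.05/2 = 0.025 and 0.05, and stop at the first failure. Every threshold is at least 0.01, so anything Bonferroni rejects, Holm rejects. The first threshold is the same, so Holm gains only once something has been rejected.

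**Holm, by simulation** (200,000 to 400,000 draws of five z-statistics; independent, or correlated 0.5). The table shows power for milk at discharge; ranges are across correlation structures.

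| Which outcomes truly improve | Bonferroni, 5 | Holm, 5 | Bonferroni, 3 primaries | Holm, 3 primaries |
|---|---|---|---|---|
| Milk at discharge only | 59% | 59% | 66% | 66% |
| Feeding outcomes only | 59% | 63% | 66% | 69–70% |
| Feeding outcomes, NEC with 30% power | 59% | 63–65% | 66% | 70–71% |
| All outcomes, 80% power each | 59% | 69–70% | 66% | 73–75% |

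If only the feeding outcomes improve, the gain is about 4 points over five outcomes and about 3 points within the primaries. If every outcome has 80% power, it is about 8 to 10 points at correlation 0.5, and about 11 for five independent tests.

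**Error rate.** With no true effects, the chance of any rejection is the same for both methods: 0.049 if independent and 0.046 if correlated.

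**The case against.** The strongest reply is that nothing here is wrong. Bonferroni is valid under any dependence, it is simple, and preferring a somewhat more powerful method can look like taste. The validity stands, and it is why this is only a suggested improvement. It is more than taste, because Holm has the same guarantee and is never worse for any outcome. The usual reason to keep Bonferroni is that it yields matching simultaneous intervals, but the article's wording ("reported with 95% CIs and Bonferroni-corrected p values") attaches the correction to the p values only.

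A second reply is that the family is left open and may be settled in an analysis plan that is not shown. That is so, and its absence is not raised as a fault. Each outcome also has both a step and a trend term, so the number of tests could be larger still. Holm's advantage holds for any family size; only its magnitude changes.

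A third reply is that the large gains do not fit the plan. The all-outcomes row gives NEC 80% power, which sits badly with the article's own statement that NEC power is limited. This stands, so the feeding-only row is the realistic guide.

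Stronger readings that a reader might infer:

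- That the secondary outcomes dilute the primary ones. This holds only if all five form one family, which the article does not say. With separate families, the primaries lose nothing to the secondaries.
- That the overlap between outcomes (severe within any NEC, exclusive within any milk feeding) argues for Holm. It does not, because Holm makes no use of correlation.
- That the power calculation ignored the correction. The match at unadjusted 0.05 suggests this but does not prove it, since the significance level and method are not given.

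**Conclusion.** The point holds as a free improvement. On either reading of the family, Holm keeps the family-wise error and never rejects less than the planned correction. The realistic gain is about 3 to 4 points of power per feeding outcome. It is near zero if only one outcome changes, and about 8 to 10 points only if all outcomes are well powered. These sizes rest on an assumed 80% starting power, a two-sided family-wise 0.05, equal effects among the improving outcomes, and correlations of 0 or 0.5. That Holm is never worse rests on none of these. The planned analysis does not inflate the error rate, and no conclusion drawn from it would be invalid.

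**What to change.** In the Multiple testing section, replace *Bonferroni-corrected p values* with *Holm-adjusted p values* and leave the 95% confidence intervals as they are. The adjusted value for the i-th smallest of m p values is the largest of (m − j + 1) × p(j) over j ≤ i, capped at 1.

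The change is one phrase and uses p values that will be computed anyway. It should be made before the outcome results are seen. The one thing given up is a simple set of simultaneous intervals matching the adjusted p values, which the article does not say it will report. No testing order between primary and secondary outcomes is needed. Making the secondary outcomes wait until all three primaries are significant would hold both of them back behind severe NEC, one of the NEC outcomes for which the article expects limited power, and it is not proposed here.

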#### Secondary analyses

In addition to the ITS analysis, we will use multivariable logistic regression to conduct a conventional before-after comparison of the odds of each primary and secondary outcome, adjusted for a range of potential confounders measured at the level of the infant, mother and unit. We will include data from both EMNODN and control units and assess whether there is any effect modification by study group. We will use a robust variance estimator to account for the clustering of infants within units and by mother.

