## Introduction

Necrotising enterocolitis (NEC) is a serious, life-threatening disease in preterm infants.^1^ An estimated 12% of infants born weighing <1500 g develop NEC and 30% of these die.^2^ Survivors have increased risk of adverse neurodevelopmental outcomes, including cerebral palsy and cognitive impairment.^3^ Encouraging and supporting own mother’s milk feeding prevents NEC and has several additional advantages, including improved long-term neurodevelopment and parent–infant bonding.^4^ Health economic analysis estimates that if all premature infants were to be fed own mother’s milk, the total lifetime cost saving to the National Health Service (NHS) would be £46.7 million (£30.1 million in the first year of life), and there would be 238 fewer deaths per year with a gain of £153.4 million in lifetime productivity.^5^

Neonatal critical care services in England are commissioned by NHS England and managed within 11 neonatal operational delivery networks, to ensure that babies and their families receive high-quality, equitable and accessible care. The East Midlands Neonatal Operational Delivery Network (EMNODN^6^) comprises 11 neonatal units across seven NHS trusts, covering an area of 15 627 km^2^, a total population of approximately 4.9 million^7^ and approximately 47 000 live births per year.^8^ In 2022, EMNODN units provided 50 443 days of care in total to infants born preterm, or unwell at term, who needed specialist neonatal care; 476 infants were cared for who were born before 32 weeks’ gestational age (GA) and survived at least 48 hours.^9^

The rate of NEC in the EMNODN has remained above the national average since 2017, when this measure was added to the National Neonatal Audit Programme (NNAP).^10^ Additionally, there are wide variations between the 11 units that comprise the EMNODN. Rates of any breastmilk feeding at discharge from EMNODN units have been consistently below the national average, again with wide local variations.

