### Setting

Workstream 1: Neonatal units in England and Wales, comparing infants admitted to the 11 neonatal units in the EMNODN with infants admitted to all other units.

Workstream 2: The 11 neonatal units that comprise the EMNODN.

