We will aggregate outcomes by month of birth (or by 2-month period if necessary to improve statistical power, without detriment to interpretation of results) and plot time series graphs to show the number of cases of each outcome per month over the study period in the EMNODN units combined. We will use a quasi-Poisson generalised additive mixed model^28^ to estimate an incidence rate ratio (IRR) for changes in the incidence of the outcomes in EMNODN units during the evaluation phase, relative to the pre-implementation period. Data for the 4-month implementation phase will be plotted graphically but excluded from statistical modelling as this period is too short to be able to model changes in incidence compared with the pre-implementation period. We will similarly plot and model data for infants admitted to units in the control group, to assess whether there are any changes in the IRR to exclude confounding due to other events or interventions which occurred around the time that the care bundle was introduced.

We will incorporate several covariates into our models as follows:

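### With 11 treated units, the robust variance planned for the EMNODN-versus-control interaction needs a small-sample correction; used uncorrected, a nominal 5% test rejects about 8 to 13% of the time

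*Protocol article*

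**What the plan says.** The Setting section defines the comparison as "comparing infants admitted to the 11 neonatal units in the EMNODN with infants admitted to all other units". The number of control units is not given.

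In the interrupted time series (ITS) analysis, the control data are handled in parallel: "We will similarly plot and model data for infants admitted to units in the control group". The purpose is to see whether the control rate ratio also changes. No contrast between the two rate ratios is described.

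The Secondary analyses section adds a "conventional before-after comparison of the odds of each primary and secondary outcome" by multivariable logistic regression. It continues: "We will include data from both EMNODN and control units and assess whether there is any effect modification by study group". In a before-after model, that is a period-by-group interaction. For its precision the section says: "We will use a robust variance estimator to account for the clustering of infants within units and by mother".

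No finite-sample correction, degrees of freedom or reference distribution is named for this model. No significance level is set for the interaction either: the Multiple testing section speaks only of incidence rate ratios.

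**The concern.** Cluster-robust variances are justified by a large number of clusters. For this interaction the count that matters is the number of treated clusters, 11, and not the total. With few treated clusters the uncorrected sandwich is too small on average, and also too variable for a normal reference. Confidence intervals are then too narrow and p values too small.

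The interaction is the only place in the article where EMNODN and control units are contrasted within one model, and the workstream 1 objective is comparative. An over-precise interaction could therefore be read as evidence of a bundle effect beyond the national change when there is none.

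**Working it through.** The article states no error rate or power for this interaction, so there is no published figure to reproduce.

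**Inputs from the article**
- Treated units: 11 (Introduction, Setting).
- Periods: January 2016 to August 2022 is 80 months; January to September 2023 is 9 months (Time period).
- Volume: 23 infants a month at 55% prevalence, read as infants receiving own mother's milk, gives 23/0.55 ≈ 42 eligible infants a month. Cross-checks: 3 NEC cases at 7% gives 3/0.07 ≈ 43; 476 infants in 2022 gives 476/12 ≈ 40 (Sample size calculation, Introduction).
- Outcomes: 3 primary + 2 secondary = 5.

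**Assumptions**
- Control units: 170, with 100, 140 and 180 also tried.
- Severe NEC rate: 3%.
- Coefficient of variation (CV) of unit size: 0 to 1.1.
- Logit-scale SDs: between units 0 to 0.4; unit-by-period 0 to 0.4.

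**Step 1: which units drive the variance.** With equal-sized units and equal between-unit spread, the treated share of the interaction variance is (1/11)/(1/11 + 1/m) for m control units. For m = 100 this is 0.90, for m = 170 it is 0.94, and for m = 180 it is 0.94. More controls cannot make up for 11 treated units.

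**Step 2: analytic size.** With k equal treated units and many controls, the uncorrected sandwich has expectation about (k−1)/k of the true variance, and the statistic behaves like t on k−1 degrees of freedom. Hence

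size = 2·P(t on k−1 df > 1.96·√((k−1)/k)).

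- k = 11: 1.96·√(10/11) = 1.869, and 2·P(t10 > 1.869) = 9.1%, or 1.8 times nominal.
- If unequal sizes leave 8 effective units: 10.9%.
- If they leave 6: 13.4%.

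**Step 3: simulation under no effect.** Logistic group-by-period model, 8,000 replicates per setting, outcome rates 0.55, 0.07 and 0.03. About 42 × 9 = 378 EMNODN infants fall in the evaluation period, or 34 per unit if equal. The ordinary sandwich used the G/(G−1) factor, G being the total number of units.

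| CV of unit size | Ordinary sandwich, z | Ordinary sandwich, t10 | Jackknife, t10 |
|---|---|---|---|
| 0 | 7.7–9.1% | 4.7–6.9% (CV 0–0.5) | 3.4–5.3% (CV 0–0.5) |
| 0.5 | 8.5–10.3% | as above | as above |
| 0.8 | 10.0–13.1% | 6.6–9.0% | 4.6–6.4% |
| 1.1 | 11.6–16.9% | 7.7–12.0% | 5.0–7.8% |

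Referring the ordinary statistic to t with degrees of freedom from the total number of units changes little. With 100, 140 or 180 control units the ordinary test gave 11.0 to 11.6% (prevalence 0.55, CV 0.8, unit SD 0.4, unit-by-period SD 0.2). The Monte Carlo standard error at 11% is √(0.11 × 0.89/8000) ≈ 0.35 percentage points.

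**Step 4: would Bonferroni help?** If a correction over five outcomes were applied to the interaction, the nominal level would be 1%. The simulated size of the ordinary test was then about 2.2 to 7.7%.

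The simulation omits covariate adjustment, multiple imputation and clustering by mother.

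**The case against.** The strongest reply is that the article names a class of estimator and not a member of it. Jackknife and bias-reduced sandwiches are robust variance estimators too, and the choice among them is the kind of detail an analysis plan, not shown here, could settle. This stands in part. A reader might infer that the plan has chosen the uncorrected form; the text does not say so, and the point must be put conditionally. It does not dissolve the point, because the article commits to a method for a contrast with 11 treated clusters, and that method in its plain default form over-rejects.

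The second reply is that the analysis is secondary. This also stands. A reader might take the interaction to be the one formal test on which the bundle conclusion rests. The article says only that it will "assess whether there is any effect modification by study group". It sets no level or decision rule, repeats the assessment for five outcomes, and gives modelling of the control series in the ITS as its check on concurrent change. The ITS rate ratios do not use this variance.

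Third, the size of the inflation depends on unstated quantities. That is true of the figures above about 9%. The 9.1% needs only 11 equal treated units and many controls.

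Finally, a change common to the whole treated network cannot be separated from the bundle in this contrast. That is a question of identification, which a variance correction does not address, and it forms no part of this point.

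**Conclusion.** The concern holds in conditional form. If the usual uncorrected sandwich with a normal reference is used for the period-by-group interaction, nominal 5% tests reject about 8 to 9% of the time with equal-sized units and about 10 to 13% at a size CV of 0.8. Some inflation appeared in every setting tried. The upper figures rest on assumed unit sizes and between-unit SDs; the assumed number of control units matters little.

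A flat statement that the plan doubles its false-positive rate goes further than the article allows: the estimator is not fully specified, no level is set, and with equal units the inflation is 1.5 to 1.8 times. The effect is confined to the secondary comparative analysis, where it makes the evidence for a change beyond the national one look firmer than it is.

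**What to change.** Specify, for the period-by-group interaction, a small-sample-corrected cluster-robust variance at unit level: for example a delete-one-unit jackknife or bias-reduced sandwich, with t on about 10 degrees of freedom or Satterthwaite degrees of freedom. Changing the reference to t10 while keeping the ordinary sandwich is only a partial repair once units are unequal (6.6 to 9.0% at CV 0.8).

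Of these options only the jackknife with t10 was simulated. It gave about 3.5 to 6.5% up to CV 0.8 and up to about 8% at CV 1.1, so it comes close to the nominal level without guaranteeing it when a few units hold most infants. Reporting the unit sizes would show readers which case applies.

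The cost is a software option and wider intervals. With 11 equal units the corrected half-width is 2.228 standard errors, against 1.869 on average for the uncorrected form, a ratio of 2.228/1.869 ≈ 1.19. No new data or design change is needed.
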